## Abstract

**Background:**

Knee osteoarthritis (OA) is a prevalent chronic musculoskeletal condition with no cure. Pain is the primary symptom and results from a complex interaction between structural changes, physical impairments and psychological factors. Much evidence supports the use of strengthening exercises to improve pain and physical function in this patient population. There is also a growing body of research examining the effects of psychologist-delivered pain coping skills training (PCST) particularly in other chronic pain conditions. Though typically provided separately, there are symptom, resource and personnel advantages of exercise and PCST being delivered together by a single healthcare professional. Physiotherapists are a logical choice to be trained to deliver a PCST intervention as they already have expertise in administering exercise for knee OA and are cognisant of the need for a biopsychosocial approach to management. No studies to date have examined the effects of an integrated exercise and PCST program delivered solely by *physiotherapists* in this population. The primary aim of this multisite randomised controlled trial is to investigate whether an integrated 12-week PCST and exercise treatment program delivered by physiotherapists is more efficacious than either program alone in treating pain and physical function in individuals with knee OA.

**Methods/design:**

This will be an assessor-blinded, 3-arm randomised controlled trial of a 12-week intervention involving 10 physiotherapy visits together with home practice. Participants with symptomatic and radiographic knee OA will be recruited from the community in two cities in Australia and randomized into one of three groups: exercise alone, PCST alone, or integrated PCST and exercise. Randomisation will be stratified by city (Melbourne or Brisbane) and gender. Primary outcomes are overall average pain in the past week measured by a Visual Analogue Scale and physical function measured by the Western Ontario and McMaster Universities Osteoarthritis Index subscale. Secondary outcomes include global rating of change, muscle strength, functional performance, physical activity levels, health related quality of life and psychological factors. Measurements will be taken at baseline and immediately following the intervention (12 weeks) as well as at 32 weeks and 52 weeks to examine maintenance of any intervention effects. Specific assessment of adherence to the treatment program will also be made at weeks 22 and 42. Relative cost-effectiveness will be determined from health service usage and outcome data.

**Discussion:**

The findings from this randomised controlled trial will provide evidence for the efficacy of an integrated PCST and exercise program delivered by physiotherapists in the management of painful and functionally limiting knee OA compared to either program alone.

**Trial registration:**

Australian New Zealand Clinical Trials Registry reference number: ACTRN12610000533099

## Background

Knee osteoarthritis (OA) is a prevalent chronic musculoskeletal condition [1] associated with pain, physical and psychological dysfunction, and reduced quality of life in affected individuals [2,3]. In addition to the personal burden of knee OA, there are substantial direct and indirect health care costs making knee OA a major public health problem [4]. Given the extent of the problem and the fact that the prevalence of OA will escalate with the ageing population and increases in obesity rates [5], effective treatment strategies are required. In particular strategies that promote long-term self-management are important given the chronicity of the condition.

Pain is the primary symptom of knee OA and people with higher levels of pain have lower levels of physical function, greater functional decline and reduced quality of life [6]. Individuals with painful knee OA experience difficulty performing basic daily activities such as shopping, performing household chores, stair climbing as well as engaging in social and outdoor activities [7]. Furthermore, knee pain related to OA is one of the strongest predictors of employment status and productivity [8]. Reducing pain is therefore a relevant and important treatment aim for this patient group.

The experience of pain is influenced by a multitude of structural, physical, and psychosocial factors [6,9,10]. Whilst stimulation of nociceptors in the capsule, subchondral bone, ligaments and other joint tissues contribute to the perception of pain, structural damage in knee OA is in fact not well correlated with pain severity [11]. Instead, physical and psychological impairments that are commonly found in this patient population are more important predictors of pain. Muscle weakness, particularly of the quadriceps, is associated with higher levels of pain and greater declines in physical dysfunction [10,12]. Psychological impairments including pain catastrophising [13], poor pain coping strategies [14], anxiety [15], depression or depressed mood [15,16] and social isolation [16] are also related to increased pain levels in people with knee OA. Furthermore, bi-directional relationships exist between pain and physical and psychological impairments whereby pain can influence, and in turn be influenced by these factors [17], leading to a downward cascade in physical and mental functioning. Given the importance of both physical and psychological impairments, it would seem logical that treatments should address both aspects in order to maximise patient outcomes.

Clinical guidelines advocate conservative non-drug strategies for the treatment of knee OA [18,19]. In particular, exercise including muscle strengthening is recommended [20] and is supported by considerable research evidence [21,22]. A recent systematic review included 18 randomised controlled trials, the majority of which involved home-based programs of quadriceps or lower limb muscle strengthening. The results showed significant improvements in pain and self-reported physical function with muscle strengthening exercise [22]. However, despite consistent findings of short-term improvements with exercise, reduced adherence to exercise programs limits long-term effectiveness [21,23]. Thus, interventions that facilitate long-term exercise adherence are needed.

Whether strengthening exercise also improves psychological parameters in people with knee OA is less clear as few studies include adequate assessment of such parameters [24-26]. There is some evidence from randomised controlled trials that strengthening exercise is associated with reductions in depressive symptoms [27] in those with knee OA [28] and in other chronic conditions [29,30]. Such exercise has also been shown to improve self-efficacy, fatigue symptoms, and sleep quality in depressed older adults [31]. Based on this limited evidence, it appears that strengthening exercise may improve some aspects of psychological functioning in those with knee OA but further research is needed.

As psychological factors are related to pain, psychological interventions are worthy of attention. Of the psychological interventions that have been considered, pain management, based on the principles of cognitive behavioural therapy, is the most extensively researched intervention in chronic pain conditions and has the strongest evidence base. One such approach, Pain Coping Skills Training (PCST) focuses on self-management and is well recognized as an effective cognitive behavioural treatment for disease-related pain conditions [29,30,32,33]. However, a meta-analysis identified only two clinical trials involving PCST in those with knee OA. Both trials showed improvements in pain and physical function over a 12 week intervention period [24,34,35] with benefits appearing to diminish over time. Given the potential benefits of PCST and yet the limited evidence in people with knee OA, further research is needed to investigate its efficacy.

In accordance with a biopsychosocial approach to the management of chronic pain [36] both physical and psychological impairments should be addressed in people with knee OA. The studies that have tested integrated exercise and psychological treatments in a variety of other chronic conditions including cancer [32,33], low back pain [29] and fibromyalgia [30] have shown positive results. Only one study has examined the effects of a combined program of PCST and exercise on pain in those with knee OA [24]. This study compared a 12 week intervention of spouse-assisted PCST alone, exercise training alone, spouse-assisted PCST and exercise training or standard care in 72 participants with knee OA [24]. The results showed that the combined program improved physical fitness, strength, pain coping and self-efficacy. In addition, those with improvements in self-efficacy were more likely to improve in psychological functioning. However, the combined intervention required participants to attend a total of four hours per week of therapy delivered by two different health professionals, in addition to home practice. From a practical perspective this requires a considerable time commitment from patients and involves substantial treatment costs that would not necessarily be sustainable in everyday practice. Research investigating other methods of delivering combined treatments is required.

PCST is generally delivered by a psychologist specialising in pain management. However, it may be beneficial to utilise a single health care professional such as a physiotherapist to deliver an integrated physical and psychological intervention [37,38]. Potential advantages of using a single therapist include better integration of the intervention components, increased availability of PCST treatment to those who may not have access to a psychologist, reduced time and cost for patients and reduced overall costs to the health care system. Although physiotherapists do not have formal training in pain management they are a logical choice to be trained in the delivery of PCST given their expertise in administering physical treatments to treat pain and their understanding of the biopsychosocial approach. No studies to date have examined the effects of an integrated exercise and formal PCST program delivered by physiotherapists in this patient population.

This project primarily aims to compare the efficacy of a 12-week integrated PCST and exercise program delivered by physiotherapists to treat pain and physical function in individuals with knee OA compared to PCST or exercise programs alone. The secondary aims of the study are to compare the efficacy of these programs on functional performance, psychological parameters, quality of life, muscle strength, physical activity levels and cost-effectiveness and to examine longer-term outcomes over a 9-month follow up period.

### Primary hypothesis

H1: A 12-week integrated intervention of exercise and PCST will be more efficacious in improving pain and self-reported physical function than a 12-week intervention of either PCST or exercise alone immediately following the intervention.

### Secondary hypotheses

H2: An integrated intervention of exercise and PCST will be more efficacious in improving pain and self-reported physical function than either PCST or exercise alone at 32 weeks and 52 weeks.

H3: An integrated intervention will be more efficacious in improving psychological function, functional performance, quality of life, physical activity levels and perceived response to treatment than either PCST or exercise alone immediately following the intervention and at 32 weeks and 52 weeks.

H4: Exercise will lead to greater improvements in muscle strength than PCST; PCST will lead to greater improvements in psychological parameters than exercise; and an integrated intervention will lead to greater improvements in both strength and psychological parameters at measured time points.

H5: Adherence to exercise during the 9-month unsupervised follow-up period will be greater with an integrated intervention than with an intervention of exercise alone.

H6: An integrated intervention will be more cost-effective than an intervention of exercise or PCST alone when costs are compared and related to the effects of the intervention at 52 weeks.

H7: Specific patient baseline characteristics will moderate or predict treatment effects while pre- to post-treatment changes in the targeted cognitions, behaviours and physical impairments will mediate the effects of PCST and exercise on subsequent patient pain and disability.

## Methods/design

### Trial design

This will be an assessor-blinded, 3-arm randomised controlled trial of a 12-week intervention involving 10 physiotherapy visits together with home practice. Measurements will be taken at baseline and immediately following the intervention (12 weeks) as well as at 32 weeks and 52 weeks to examine maintenance of any intervention effects. Specific assessment of adherence to the treatment program will also be made at weeks 22 and 42. The study will be conducted at two sites, Melbourne and Brisbane, Australia to facilitate generalizability of the results and to ensure timely recruitment. The protocol will conform to CONSORT guidelines for reporting non-pharmacological interventions [39] and has been registered with the Australia and New Zealand Clinical Trials Registry prior to study commencement.

### Participants

We will recruit participants with painful knee OA from the community in the Melbourne and Brisbane metropolitan regions. A number of recruitment strategies will be used including (i) advertising through local clubs, community centers, newspapers, Australian Health Management, Arthritis Australia and University websites, University staff newsletters, radio, and Facebook; (ii) placing brochures and study posters in medical and physiotherapy clinics; (iii) conducting presentations about knee OA in the local community, and (iv) using our database of people who have been recruited from the community for prior studies and have given consent for future contact.

To be eligible, participants must fulfill the following criteria:

i. Aged ≥ 50 years;

ii. Knee OA fulfilling American College of Rheumatology classification criteria [40] of knee pain on most days of the past month and tibiofemoral osteophytes on x-ray (Kellgren and Lawrence ≥ Grade 2) [41];

iii. Knee pain for ≥ 3 months;

iv. Overall average knee pain in the last week ≥ 40 on a 100 mm Visual Analogue Scale (VAS);

v. Western Ontario and McMaster Universities (WOMAC) Osteoarthritis Index physical function score of ≥ 25 indicating at least a moderate level of difficulty in performing activities of daily living.

The exclusion criteria are:

i. Knee surgery including arthroscopy within the past 6 months;

ii. Awaiting or planning any back or lower limb surgery within the next 12 months;

iii. Current or past (within 3 months) oral or intra-articular corticosteroid use;

iv. Systemic arthritic conditions such as rheumatoid arthritis;

v. Physiotherapy, chiropractic or acupuncture treatment or exercises specifically for the knee within the past 6 months;

vi. Walking >30 min continuously daily or participating in a regular (more than twice a week) exercise program;

vii. Past participation in a PCST program;

viii. Inability to walk unaided as this is necessary for some of the physical testing;

ix. Medical condition precluding safe exercise such as uncontrolled hypertension or heart condition;

x. Self-reported psychiatric history such as schizophrenia;

xi. Self-reported diagnosis of current clinical depression;

xii. Neurological condition such as Parkinson’s disease, Multiple sclerosis or stroke;

xiii. Inadequate written and spoken English;

xiv. Unable to comply with the protocol such as inability to attend therapy sessions or attend assessment appointments at the University.

### Procedure

The procedure is outlined in Figure 1. Preliminary screening will be conducted over the telephone by a research assistant not involved in outcome assessment. Volunteers who are deemed potentially eligible will undergo a semiflexed posteroanterior x-ray of their painful knee (the more symptomatic knee in cases of bilateral eligible knee pain) at one of six trial radiology centres unless they can provide their own such films from within the previous 12 months. X-ray grading will be performed by two trained researchers at each site and any disagreement will be resolved through discussion or where necessary, by a third rater. A screening record will be maintained to document the criteria eliminating those found to be ineligible. Participants will attend the University of Melbourne or the University of Queensland for baseline testing, following which they will be randomised into one of three intervention groups: (i) exercise; (ii) PCST; or (iii) integrated exercise and PCST. Each intervention will last for 12 weeks and will involve 10 individual visits to a project physiotherapist together with home exercise and/or pain coping skills practice. Following the intervention, participants will continue their home exercise and/or pain coping skills practice unsupervised for nine months. Participants will be re-assessed at week 12 (immediately following the intervention), at week 32 (by postal questionnaires) and at week 52 (at the University). Additional questionnaires relating to home practice adherence will also be collected at weeks 22 and 42. Participants will also wear a pedometer for 7 consecutive days at baseline, 12 weeks and 52 weeks. All participants will be asked to refrain from seeking other forms of treatment during the trial. However, due to ethical considerations, analgesia and non-steroidal anti-inflammatory drugs will be permitted as required.

**Figure 1 F1:**
[figure not shown]
**Diagram of study protocol**
.

Ethics approval has been obtained from the University of Melbourne Human Research Ethics Committee (HREC: 1033341) and Radiation Safety Human Services and from the University of Queensland Medical Research Ethics Committee (MREC: 2010000340) and Radiation Protection Advisor. All participants will provide written informed consent.

### Blinding

The outcome assessors at both sites will be blind to group allocation and will not be involved in providing the interventions nor will they visit any of the physiotherapy treatment centers. Participants will be requested not to disclose details about their treatment to the outcome assessors. The physiotherapists as well as the psychologists and researchers managing the study at both sites are by necessity unblinded. The statistician will be blind to group allocation until completion of the statistical analyses.

### Randomisation and allocation concealment

The randomisation schedule will be prepared by the study biostatistician using a computer generated random numbers table. Randomisation will be conducted by random permuted blocks of size from 4 to 6 stratified by site (Melbourne or Brisbane) and gender (male or female). To conceal randomisation, an independent staff member will prepare consecutively numbered, sealed, opaque envelopes for each site. The envelopes will be kept in a locked location at each site accessible only by an unblinded researcher. Each envelope will be opened in sequence once the participant has completed the baseline measurements by a person not involved in participant recruitment. An unblinded researcher will then schedule the participants’ first appointment with their treating physiotherapist.

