### Sample size

The two primary endpoints are knee pain measured on the VAS and WOMAC physical function score. The minimum clinically important difference to be detected in OA trials is a change in pain of 18 mm (on 100 mm VAS) [44] and a change of six physical function WOMAC units (out of 68) [73]. Based on our previous data, we assume a common between-participant standard deviation of change of 30 mm for pain and 12 units for WOMAC physical function. These statistics indicate a smaller standardized effect size of interest (Cohen’s *d*) of 0.5 for the WOMAC measure than the *d* of 0.6 for pain. Since primary analyses will adjust for baseline of the outcome measure by ANCOVA, the sample size to detect the above effect sizes with 80% power taking into account a pre-post correlation of 0.50 is 48 patients per arm for WOMAC function and 33 per arm for VAS pain. We obtained the pre-post correlation from data from Lim et al., in which correlations of 0.58 and 0.77 were observed for pain and function respectively [74], and therefore our value of 0.50 is expected to be conservative. A further issue is that comparisons of the exercise alone arm with each of the PCST arms involve separate physiotherapists per arm and therefore clustering effects by physiotherapists need to be accounted for in the sample size and analysis. Prior data indicate that the intra-physiotherapist correlation for pain and function is likely to be at most 0.050 [74]. Assuming physiotherapists will each treat on average 7 patients (hence clustering design effect = 1 + 6*0.050 = 1.30), a total sample size of 63 patients per arm is required. Assuming 10% dropout increases the sample size to 70 per arm, or 10 physiotherapists treating 7 patients each. Slight loss of power is expected due to imbalances in number of patients per physiotherapist; however with access to 11 physiotherapists in the PCST arms this should be negated. The comparison of Exercise and PCST versus PCST alone arms will be performed ‘within-physiotherapist’ and hence does not suffer from these clustering effects. With 70 patients per arm the power is 93% to detect the WOMAC effect size and 98% for pain.

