### Statistical analysis

Comparisons will be performed using an intention-to-treat analysis using all randomized participants. This analysis will include all participants including those who have missing data and those who are not fully adherent to the protocol. Some attrition is anticipated despite the fact that we will implement procedures to minimize loss to follow-up and participant withdrawal, and maximize adherence. We will employ multiple imputation methods to handle missing data in the analyses. Standard diagnostic plots will check model assumptions. Effect sizes will be calculated with an effect size of 0.2 being small, 0.5 medium and 0.8 large. All tests will be two-tailed and carried out at the 5% significance level.

Demographic and clinical characteristics as well as baseline data will be presented to assess the baseline comparability of the intervention groups. These variables will also be examined for those participants who withdraw from the study. Descriptive statistics will be presented for each group as mean change (standard deviation, 95% confidence intervals) in the two primary outcomes from baseline to 12 weeks. Between-group mean differences and 95% confidence intervals will be estimated with a mixed effects linear regression model in which physiotherapists are treated as random effects and baseline scores of the primary outcome are entered as the covariate [75], together with adjustment for the stratification variables of site and gender. Secondary outcomes will be as above for normally distributed measures, or will use binary or proportional odds random effects regression models for binary or ordinal outcomes as appropriate. Standard diagnostic plots will check model assumptions. All tests will be two-tailed and carried out at the 5% significance level with no statistical adjustment for multiple testing.

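### Block sizes of 4 to 6 do not fit equal allocation to three arms: only 6 is a multiple of three, and no rule is given for the surplus places (a minor error that leaves the sample size intact)

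*Protocol article*

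**What the plan says.** - **Three arms.** The Abstract (Methods/design) has participants "randomized into one of three groups: exercise alone, PCST alone, or integrated PCST and exercise", and Trial design confirms it: "This will be an assessor-blinded, 3-arm randomised controlled trial of a 12-week intervention involving 10 physiotherapy visits together with home practice".
- **Block sizes.** Randomisation and allocation concealment specifies "random permuted blocks of size from 4 to 6 stratified by site (Melbourne or Brisbane) and gender (male or female". Two sites by two genders makes four strata.
- **Equal arms.** Sample size states: "Assuming 10% dropout increases the sample size to 70 per arm". The article gives no allocation ratio in words, but this implies 1:1:1 and 210 patients in all. No section plans an unequal ratio.
- **Surplus places.** No section says how a block of 4 or 5 is divided among three arms.

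**The concern.** Permuted blocks are used so that every completed block returns the arms to the planned ratio. With three equal arms, that happens only if the block size is a multiple of three. At least one size in the stated range fails, whether the range means 4, 5 and 6 or only 4 and 6. This is not a detail left to a fuller document: the article states the sizes, and they do not fit its own design.

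Two things are at stake. Arm sizes, overall and within strata, can drift further apart than blocking should allow, which costs some power. The schedule also cannot be reproduced from the text, because the rule for surplus places is undefined.

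**Working it through.** **1. The plan's own sample size.** Inputs from Sample size: d = 6/12 = 0.5 for WOMAC function and 18/30 = 0.6 for pain; pre-post correlation r = 0.50; 80% power; design effect 1 + 6 × 0.050 = 1.30; dropout 10%. The two-sided 5% level is from Statistical analysis.

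n per arm = 2(z₀.₉₇₅ + z₀.₈₀)²(1 − r²)/d², with (1.960 + 0.842)² = 7.849 and 1 − r² = 0.75:
- Function: 2 × 7.849 × 0.75/0.25 = 47.1, so 48 (stated 48).
- Pain: 2 × 7.849 × 0.75/0.36 = 32.7, so 33 (stated 33).
- Clustering: 48 × 1.30 = 62.4, so 63 (stated 63).
- Dropout: 63/0.9 = 70 (stated 70).
- Unclustered power at 70 v 70: 92.7% and 98.4% (stated 93% and 98%).

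Every figure reproduces, and all of them assume equal arms.

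**2. Divisibility.**

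| Block size | Remainder on division by 3 | Best possible split |
|---|---|---|
| 4 | 1 | 2:1:1 |
| 5 | 2 | 2:2:1 |
| 6 | 0 | 2:2:2 |

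**3. Effect on arm sizes.** I simulated 20,000 schedules of 210 patients in four strata. My assumptions, which the article does not give, are that each block size is equally likely, that surplus places go to arms drawn at random, and that the strata hold 52/53/52/53 or 42/63/42/63 patients. Ranges below cover both stratum patterns.

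| Block sizes | Largest minus smallest arm: median | 95th percentile | Exactly 70/70/70 |
|---|---|---|---|
| 4, 5, 6 | 5 | 11 | about 3% |
| 4, 6 | 5 | 9 to 10 | about 3% |
| 3, 6 | 2 | 3 to 4 | 16% to 44% |
| 6 only | 2 | 4 | 14% to 22% |
| 6, 9 | 2 | 4 to 5 | 12% to 20% |
| No blocking | 13 | 28 | not tabulated |

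With sizes 4, 5 and 6 the smallest arm averages about 67, and its 5th percentile is 64.

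**4. Effect on power.** For the clustered WOMAC function comparison after 10% dropout, power = Φ(d/SE − 1.96), with SE = √[0.75 × 1.30 × (1/m₁ + 1/m₂)] and m = 0.9n.
- 70 v 70 (m = 63, 63): SE = 0.1759, d/SE = 2.842, power 81.1%.
- 67 v 72 (m = 60.3, 64.8): d/SE = 2.830, power 80.8%.
- 64 v 70 (m = 57.6, 63): SE = 0.1800, d/SE = 2.778, power 79.3%.

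The typical loss is therefore 81.1 − 80.8 = 0.3 points, and an unfavourable draw loses 81.1 − 79.3 = 1.8 points. Without clustering or dropout, the WOMAC comparison goes from 92.7% at 70 v 70 to 91.6% at 64 v 70.

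**The case against.** The best defence is that very little is lost, and most of it stands. Random surplus places introduce no bias. Blocks of 4 to 6 still balance far better than no blocking (95th percentile of the gap 11, against 28). The primary model adjusts for site and gender. Multiples of three do not guarantee exactly 70 per arm either, because the last block in each stratum may be incomplete, and 70 is in any case a planning target. It may also be no more than a slip in a condensed article, with a sound schedule behind it.

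None of this reconciles the stated sizes with three equal arms. It limits the weight of the point without removing it.

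A reader might infer two stronger things, and the article supports neither.
- **Grossly unequal arms.** If sizes 4 and 6 were used equally often and the extra place always went to the same arm, 21 blocks of each would give 21 × 2 + 21 × 2 = 84 in that arm and 21 × 1 + 21 × 2 = 63 in each of the others. Nothing in the article describes such a fixed pattern. It describes random permuted blocks from a computer-generated schedule.
- **Upset physiotherapist caseloads.** The average of 7 patients per physiotherapist is not set by block size. Under Interventions, participants choose their physiotherapist by geographical availability, and Sample size already allows for uneven numbers per physiotherapist.

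**Conclusion.** The point holds as a minor design or reporting error. It is certain that the stated block sizes do not fit a three-arm trial with equal allocation, and that no rule for surplus places is given. That conclusion needs no assumption.

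The size of the effect does rest on assumptions: random surplus places, equally likely block sizes and the stratum sizes tried. Under these, the typical gap between the largest and smallest arm rises from about 2 to about 5, and power in the tightest comparison falls by about 0 to 2 points. It can dip just under 80% in an unfavourable draw. There is no bias, most of the balance is kept, and the planned 70 per arm is correctly derived.

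**What to change.** State 1:1:1 allocation with randomly varying block sizes that are multiples of three, with equal numbers per arm in every block and a separate list for each site-by-gender stratum.

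Sizes 6 and 9 are preferable to 3 and 6. In a block of 3 the last allocation follows from the first two, and the Blinding section says that the physiotherapists and managing researchers are unblinded. The price is slightly more imbalance from incomplete last blocks: the 95th percentile of the gap is 4 to 5, against 3 to 4 with 3 and 6.

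Then check the schedule actually in use:
- If it already uses multiples of three, correct the sentence.
- If it does not, regenerate the unused part of each list, and report the sizes used and how surplus places were assigned.
- If no envelopes remain, only the reporting applies.

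The cost is one sentence and, at most, new lists and envelopes for places not yet allocated. No patients are added and the sample size calculation is unchanged.
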